**Sample size calculation**

Sample size was calculated by G*power 3.1.9 based on the following conditions. According to Costantino's trial, the subjects of the two groups received 12 weeks of aquatic exercise and back school program respectively. The effect size was calculated to be 0.35 by using the RMDQ score of the experimental group (mean = 5.37, SD = 1.82) and the control group (mean = 6.11, SD = 2.36) during the 3-month follow-up.(Costantino & Romiti, 2014) The two groups were measured 4 times by using a mixed design of repeated measures analysis of variance. Considering that α = 0.05, power (1-β) = 0.95, Corr amongst rep measures = 0.5, the total sample size was 70. Considering the possibility of a 20% missing rate, the minimum sample size was 88. According to the calculation, 100 subjects will be expected to be recruited, and 50 subjects will be included in each group.

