**Statistical analysis**

Data will be collected and analyzed via SPSS 20.0 and Microsoft 2016. Considering that someone may drop out midway, all outcomes should be conducted by intention-to-treat analysis and per-protocol analysis. For baseline variables, we will detect the categorical variables (e.g. gender, education levels and occupation) with chi-square test and analyze the continuous variables (e.g. age, height, weight, BMI, and pain intensity) with independent t-test or Mann–Whitney U test to compare the statistical significance between the TAE group and the PTMs group. The results of descriptive statistics will be presented as mean ± standard deviation.

The experimental results were compared through adjusted two-way repeated measures ANOVA (group × time). The adjustment factors included gender, age, BMI, physical activity, LBP duration, NRS of the most severe LBP, medication, and smoking history. A chi-square test was conducted to compare the proportion of participants in each group who met the MCID for pain and function at postintervention. Although the MCID for RMDQ and NRS remains controversial, values of 5.0 and 2.0 are considered reasonable and commonly used. The χ2 test was also applied to determine the difference between the 2 groups for the proportion of participants reporting GPE, adverse events and treatment recommendations. The effect sizes were presented to measure the strength of any outcome indicators, where 0.2 ≤ Cohen’s d < 0.5 means a ‘small’ effect size, 0.5 ≤ Cohen’s d < 0.8 indicates a ‘medium’ effect size and Cohen’s d ≥ 0.8 reflects a ‘large’ effect size.

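### Intention-to-treat is promised for all outcomes, but the repeated-measures ANOVA fixed for RMDQ and the other scale scores, run as written, keeps only participants with complete data

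*Protocol*

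**What the plan says.** The Statistical analysis section of the protocol gives drop-out as its reason for analysing every outcome in two populations: "all outcomes should be conducted by intention-to-treat analysis and per-protocol analysis". The software is fixed as well: "Data will be collected and analyzed via SPSS 20.0 and Microsoft 2016". For the scale scores the method is then stated: "The experimental results were compared through adjusted two-way repeated measures ANOVA", with group and time as factors and eight adjustment factors.

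The Sample size calculation section confirms the layout: "The two groups were measured 4 times by using a mixed design of repeated measures analysis of variance". It also expects incomplete data: "Considering the possibility of a 20% missing rate, the minimum sample size was 88".

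Binary and categorical outcomes are treated differently. For the responder outcome, "A chi-square test was conducted to compare the proportion of participants in each group who met the MCID", and chi-square tests also serve global perceived effect, adverse events and treatment recommendation.

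The Interventions section counts as drop-outs those who withdraw, those absent from an assessment, and those with more than two weeks of missed sessions. No section says how a participant with an incomplete record enters the ANOVA.

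**The concern.** The promised population and the fixed method pull against each other. Classical repeated-measures ANOVA in SPSS works on one row per participant, and a row with any missing visit or covariate is deleted. Someone with a valid 3-month RMDQ but no 12-month value is lost from the 3-month comparison too, although that value was collected. The analysed set for the primary outcome is then decided by who attended all four visits, not by randomisation.

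This matters because drop-out could relate to arm and to response. Under Randomization and blinding, the protocol says that participants cannot be kept unaware of their group. Under Withdrawal criteria it lists loss of interest, timetable conflicts and side effects of either treatment. The arms are a pool exercise class and passive modalities, and Goal 2 rests on the 6- and 12-month visits.

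**Working it through.** **1. The protocol's own figures.** Inputs from Sample size calculation: "Considering that α = 0.05, power (1-β) = 0.95, Corr amongst rep measures = 0.5, the total sample size was 70", effect size 0.35, four measurements. For the between-group test, λ = f²·N·m / (1 + (m − 1)ρ), with 1 and N − 2 degrees of freedom. With f = 0.35, m = 4, ρ = 0.5 and N = 70, λ = 0.1225 × 70 × 4 / 2.5 = 13.72 and power is 0.955. At N = 68 power is 0.949. So 70 reproduces. For drop-out, 70 / 0.8 = 87.5, rounded up to 88. In reverse, 88 × 0.8 = 70.4, so the calculation aims at about 70 participants with usable data after losses, which fits a completer analysis. (Whether 0.35 is the right value to enter as f is a separate question and is not argued here.)

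**2. Who remains in the ANOVA.** The target is 100 participants.
- If the 20% means missing at least one visit: 100 × 0.8 = 80.
- Assumption: each of the three follow-up visits is missed independently with probability p. Then 100 × (1 − p)³ remain:

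| p per visit | complete records |
| --- | --- |
| 5% | 86 |
| 10% | 73 |
| 15% | 61 |
| 20% | 51 |

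Missing covariates would lower these counts further.

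**3. Power.** By the formula in step 1, N = 80 gives λ = 15.68 and power 0.974. At N = 50 to 52 power is 0.87 to 0.88. With about 80 completers, power stays above the planned 0.95.

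**4. Possible bias (illustration on assumed mechanisms).** The true difference is 6.11 − 5.37 = 0.74 at each follow-up visit, with none at baseline. The SD is √((1.82² + 2.36²)/2) = 2.11, and the correlation is 0.5 between all visits. These values come from the sample size section. Assumed: everyone is seen at month 3; 20% of each arm then leaves; and where drop-out depends on outcome, its odds rise by a fixed ratio per 3-month RMDQ point. The table gives the complete-case contrast in change from baseline (400,000 simulated per arm):

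| Outcome-dependent drop-out | Odds ratio | 3 months | 12 months |
| --- | --- | --- | --- |
| PTMs only | 1.65 | 0.55 | 0.74 |
| PTMs only | 1.35 | 0.61 | 0.74 |
| PTMs only | 1.2 | 0.66 | 0.74 |
| Both arms | 1.65 | 0.74 | 0.74 |
| TAE only | 1.65 | about 0.93 | 0.74 |

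Using every 3-month value collected gives 0.74 in all rows. The 12-month contrast holds because, with equal correlations, selection on the 3-month score shifts the baseline and 12-month means of the completers equally, so the shift cancels in the change.

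**The case against.** The strongest reply is that nothing in the protocol says that incomplete records are deleted, and no SPSS procedure is named. Intention-to-treat with ANOVA on an imputed data set would be coherent, and missing-data handling is commonly left to the statistical analysis plan, which is not shown. This stands as a limit. The point is therefore the mismatch between the stated principle and the fixed method, not the absence of an imputation plan.

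Some stronger readings are tempting but not supported:
- A reader might infer that every test loses these participants. The chi-square outcomes do not need all four visits.
- A reader might infer that the two promised analyses become nearly the same and that intention-to-treat then protects against nothing. Someone who misses many sessions but attends every assessment stays in the completer set and would presumably leave a per-protocol set. The protocol gives no figure for how many such people to expect.
- A reader might take an error of about a quarter in the 3-month contrast as the expected bias. It needs strong outcome-dependent drop-out in one arm only. The protocol lists the same withdrawal reasons for both arms, and with the same mechanism in both the bias vanishes.

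Two points also moderate the practical risk. Participant timeline plans regular contact by WeChat or phone to obtain the later data, and most adjustment factors are baseline questionnaire items, so few should be missing.

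**Conclusion.** The mismatch is real for RMDQ and the other scores analysed by ANOVA. Provided that nothing is imputed beforehand, the protocol would report a completer result as intention-to-treat: about 80 of 100 participants if 20% miss at least one visit, and fewer if 20% is a per-visit rate. Power is not the argument, at about 0.97 with N = 80 on the stated inputs. What is lost is the randomised comparison, together with 3- and 6-month data already in hand. The size and direction of any bias are unknown. In the assumed scenarios the 3-month change contrast runs from about 0.55 through 0.74 to 0.93 against a true 0.74, so the error could go against TAE, in its favour or be nil. The 12-month change contrast is nearly unbiased there, a result that rests on the equal-correlation assumption.

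**What to change.** In Statistical analysis, replace the repeated-measures ANOVA for RMDQ and the other scale scores by a likelihood-based linear mixed model (MIXED in the SPSS version already named). It should include all randomised participants and all available visits, with visit as a categorical factor, the group × visit interaction, an unstructured covariance and the same adjustment factors.

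No new data or participants are needed. The cost is a little more analysis work and reliance on a missing-at-random assumption, which should be stated. The model retains people with missed visits but not those with a missing adjustment factor, so these factors should be complete at baseline.

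Multiple imputation for the responder tables, and a sensitivity analysis that shifts imputed values for drop-outs in the unfavourable direction, are optional additions. The mismatch can be resolved without them.

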**Methods/Design**

**Research goals and hypotheses**

We will design an RCT to conclude TAE and PTMs for people with low back pain to see:

Goal 1: whether TAE compared favorably with PTM for people with CLBP;

hypotheses for Aim 1: Patients in TAE group will receive more benefits in pain relieve and functional improvement than subjects in the PTMs group. There will be significant differences between two groups.

Goal 2: whether TAE yields long-term effects.

hypotheses for Aim 2: TAE will create a long-term effect on people with CLBP while PTMs will not. There will be significant differences between two groups during the fellow-up period.

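### Baseline RMDQ is counted as one of four outcome visits instead of being used as a covariate, which leaves the group × time ANOVA valid but inefficient and poorly aimed at the two goals

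*Protocol*

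**What the plan says.** The protocol's Statistical analysis section compares results by an adjusted two-way (group × time) repeated measures ANOVA. On the adjustment it says: "The adjustment factors included gender, age, BMI, physical activity, LBP duration, NRS of the most severe LBP, medication, and smoking history". That makes eight factors. Worst pain on the NRS is among them; RMDQ is not.

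The Sample size calculation section says: "The two groups were measured 4 times by using a mixed design of repeated measures analysis of variance". It continues: "Considering that α = 0.05, power (1-β) = 0.95, Corr amongst rep measures = 0.5, the total sample size was 70".

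The Participant timeline section and Table 3 schedule RMDQ at baseline, 3, 6 and 12 months and at no other time. The Primary outcomes section names RMDQ alone and gives no primary visit.

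The Research goals and hypotheses section asks whether TAE does better than PTMs (Goal 1, no time point given) and whether the groups differ during follow-up (Goal 2).

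**The concern.** Both goals are comparisons between groups once treatment has been given. The ANOVA as described offers two tests involving group, and neither is aimed at such a comparison.

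- **Group main effect.** It averages RMDQ over all four visits. Randomisation makes the expected difference at baseline zero, so including that visit dilutes whatever difference follows.
- **Group × time interaction.** With four time levels it has 3 degrees of freedom. It responds to any difference in the shape of the two profiles and yields no estimate at the end of treatment or in follow-up.

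Baseline RMDQ is collected from everyone. As a covariate it would remove between-patient variation from the later scores; as an outcome level it adds a visit at which no treatment difference is expected. What is at stake is power, and a result that can be read directly against Goals 1 and 2.

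**Working it through.** **1. Reproduce the planned sample size.** Inputs from the Sample size calculation section: effect size 0.35, α = 0.05, power 0.95, m = 4 measurements, ρ = 0.5, two groups.

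- Between-group main effect: λ = f²·N·m / [1 + (m − 1)ρ]. With f = 0.35 and N = 70, λ = 0.1225 × 70 × 4 / 2.5 = 13.72 and power is 0.955. At N = 68 power is 0.949. So N = 70, and 70 / 0.80 = 87.5, rounded up to 88. Both stated figures reproduce.
- Group × time interaction: λ = f²·N·m / (1 − ρ). This reaches 95% at N = 20, so it is not the source of 70.

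The trial was therefore sized on the main effect over four visits, baseline included.

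**2. Effect size implied by the cited means.** Pooled SD = √[(1.82² + 2.36²)/2] = 2.107, and d = (6.11 − 5.37) / 2.107 = 0.351. In step 1 the value 0.35 acts as Cohen's f, which for two equal groups means d = 0.70. Both values of d are carried below.

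**3. Set-up.** The SD is 1 and ρ = 0.5 between any two visits. There are N = 80 evaluable participants (100 less 20%), 40 per arm. The baseline difference is 0 and the other covariates are ignored. A sustained difference d at 3, 6 and 12 months is an assumption. For d = 0.35 the mean over four visits is 3 × 0.35 / 4 = 0.2625, three quarters of 0.35.

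- (a) Interaction: λ = (N/4)·Σ(dⱼ − d̄)² / (1 − ρ) = 20 × (0.2625² + 3 × 0.0875²) / 0.5 = 3.675, on 3 and 234 df.
- (b) Main effect over four visits: λ = (N/4)·d̄² / [(1 + 3ρ)/4] = 20 × 0.0689 / 0.625 = 2.205, on 1 and 78 df.
- (c) 3-month difference adjusted for baseline: λ = (N/4)·d² / (1 − ρ²) = 20 × 0.1225 / 0.75 = 3.267, on 1 and 77 df.
- (d) Mean of the three later visits adjusted for baseline: λ = (N/4)·d² / [(1 + 2ρ)/3 − ρ²] = 20 × 0.1225 / 0.4167 = 5.88, on 1 and 77 df.

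| Scenario (N = 80, ρ = 0.5) | (a) | (b) | (c) | (d) |
|---|---|---|---|---|
| d = 0.35 sustained | 33% | 31% | 43% | 67% |
| d = 0.70 sustained | 91% | 84% | 95% | >99% |
| Builds late: 0.175, 0.26, 0.35 | 24% | 20% | about 15% | 43% |
| Fades: 0.35, 0.175, 0 | 30% | 11% | 43% | 22% |

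With 100 evaluable and d = 0.35 sustained, the figures are 40%, 38%, 52% and 77%.

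**4. Sensitivity to ρ** (N = 80, d = 0.35 sustained).

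| ρ | (a) | (b) | (c) | (d) |
|---|---|---|---|---|
| 0.3 | 24% | 39% | 37% | 64% |
| 0.7 | 52% | 26% | 58% | 79% |

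**5. Like with like.** Tests (a) to (d) do not all address the same hypothesis. The closest match for an overall difference is (b) against (d): 31% against 67%. For a 3-month difference, a change-from-baseline contrast has variance 2(1 − ρ) = 1.00 against 0.75 after covariate adjustment, and power 34% against 43%.

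**The case against.** **The planned ANOVA already uses baseline.** With baseline as a time level, the interaction tests differential change from it. Leaving baseline RMDQ off the covariate list is consistent with that model, and listing it as well would use it twice. This stands. A reader might infer that the planned test is biased or invalid; under randomisation it is neither. The point concerns efficiency and aim, and the remedy is to move baseline from one role to the other.

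**The gain is not uniform.** This also stands. If 3 months alone were primary, the gain over the interaction at d = 0.35 is about 10 points (33% to 43%), and at d = 0.70 it is 91% to 95%. If the effect builds late, the 3-month test does worse than the interaction. Testing 12 months only after a significant 3-month result would succeed on both in about 23% of trials under a sustained d = 0.35, and in about 9% if the effect builds late (simulated). If the effect fades, the adjusted mean of later visits (22%) falls below the interaction (30%).

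**Much of the low absolute power has another cause.** The sample size used 0.35 as f while the cited means give d = 0.35. That is a separate matter. The listed covariates, worst pain in particular, may also recover some precision; the protocol gives no figure for this.

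**Two further inferences are not supported.** A reader might infer uncontrolled testing at each visit, but the protocol states no visit-by-visit tests, and contrasts and multiplicity can be left to a statistical analysis plan. A reader might also take "TAE will create a long-term effect on people with CLBP while PTMs will not" as a plan to rest Goal 2 on a non-significant change within the PTMs arm. The next sentence of that hypothesis states a between-group difference during follow-up, and no within-arm test is planned.

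**Conclusion.** The point holds as one of efficiency and targeting. The visit schedule and the count of four measurements together imply that baseline RMDQ is an outcome level, although the Statistical analysis section does not say so outright. Its absence from the covariates is explicit.

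At d = 0.35 the like-for-like loss on the overall comparison is large, at 36 percentage points. It is smaller for a single 3-month comparison. At d = 0.70 the planned tests already have 84% to 91% power, so there is less to gain. These figures rest on equal correlation of 0.5 between all visits, 80 evaluable participants, a sustained effect unless stated, and no contribution from the other covariates. A statistical analysis plan might add visit contrasts, but contrasts alone would not change the role that the protocol gives to baseline RMDQ.

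**What to change.** In the Statistical analysis section:

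- Model RMDQ at 3, 6 and 12 months, with baseline RMDQ as a covariate instead of a time level.
- Treat each secondary scale the same way, with its own baseline. For worst pain on the NRS, make sure the baseline value does not enter both as covariate and as outcome level.
- Keep the other listed factors, stated as measured at baseline.
- Report from this model the between-group difference after treatment (Goal 1) and during follow-up (Goal 2), with confidence intervals.

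Which contrast is primary is the sponsor's choice and should be fixed before data are seen. Naming 3 months alone, with 12 months tested only afterwards, costs power if benefit builds late; averaging the later visits costs power if it fades.

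The change needs no extra visit, participant or measurement. It costs a rewrite of the analysis paragraph and a sample size statement that refers to the chosen contrast.

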**Inclusion criteria are as follows:**

1. Aged ranged from 18 to 65; 2. Pain, muscle tension or stiffness between the buttock band and the rib arch; may also have lower limb pain; 3. Pain intensity (when the most painful) ≥ 3 on the numeric rating scale (NRS); 4. CLBP lasting at least 3 months; 5. Voluntary participation in the trial and with written informed consent; 6. Accepted randomization. Subjects will be included if they meet all criteria above.

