**Primary outcomes**

Disability was assessed with the Roland Morris Disability Questionnaire (RMDQ), which contains 24 items that are closely related to the daily life activities of patients with CLBP.(Mbada et al., 2017) The scores are as follows: 1 for checking ‘YES’ and 0 for checking ‘NO’. The final score varies from 0 to 24. Higher scores are associated with more severe disability.(Yi et al., 2012)

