**Secondary outcomes**

1. Pain intensity was measured with the NRS, which consisted of 11 numbers from 0 to 10. The scores are set as follows: 0 as painless, 1–3 as mild pain, 4–6 as moderate pain and 7–10 as strong and unbearable pain. The subjects reported the pain intensity they feel at the present and that they experienced last week (slightest, average and most serious).(Morone, Rollman, Moore, Li, & Weiner, 2009)

2. Quality of life was measured with the Short-form (36) Health Survey (SF-36). SF-36 consists of eight scales, and a high score indicates low disability. The SF-36 questionnaire is reliable and relatively stable considering that its overall Cronbach’s α coefficient = 0.791 and r = 0.778.(Zhang, Qu, Lun, Guo, & Liu, 2012)

3. Anxiety state was measured with the self-rating anxiety scale (SAS). SAS is a 20-item self-reported assessment device.(Samakouri et al., 2012) Each question is based on the following responses: ‘rarely’, ‘sometimes’, ‘usually’ and ‘most of the time.’ A respondent should choose the appropriate statement on the basis of his condition within the past 1 or 2 weeks. The total raw score may vary from 20 to 80, a high score indicates high anxiety levels.(Samakouri et al., 2012)

4. Depression state was measured with the Zung Self-Rating Depression Scale (SDS). The SDS is a 20-item self-reported questionnaire covering affective, psychological and somatic symptoms associated with depression. Each item is scored on a Likert scale that ranges from 1 to 4. Total scores range from 20 to 80, wherein 20–44 is normal, 45–59 is mildly depressed, 60–69 is moderately depressed and >70 is severely depressed.

5. Sleep quality was measured with the Pittsburgh Sleep Quality Index (PSQI). The PSQI is a self-reported scale that is used to assess sleep quality over a 1-month period. The PSQI consists of 19 individual items and comprises 7 components that are used evaluate sleep quality from several different aspects, such as sleep latency, sleep duration, habitual sleep efficiency, sleep disturbances, sleeping medication use and daytime dysfunction. The global score of PSQI ranges from 0 to 21, wherein high values indicate poor sleep quality.(Hita-Contreras et al., 2014)

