6. The Pain Anxiety Symptoms Scale (PASS) was used to evaluate pain-induced avoidance, fear, cognitive anxiety and physiological anxiety. The PASS contains 20 items. Each item is divided into 6 grades: ‘never’, ‘occasionally’, ‘sometimes’, ‘often’, ‘almost always’ and ‘always’. The total score ranges from 0 to 100. High scores are indicative of severe pain and anxiety symptoms. The internal consistency of the scale is good with Cronbach α = 0.92 and test–retest reliability intraclass correlation coefficient (ICC) = 0.90.(XY et al., 2017)

7. Kinaesiophobia was measured with the Tampa Scale for Kinaesiophobia (TSK). The 17-item version of the TSK is used to assess the fear of activity or (re)injury resulting from pain.(Aguiar, Bataglion, Visscher, Bevilaqua Grossi, & Chaves, 2017) It is rated by using a 4-point Likert scale that varies from ‘strongly disagree’ to ‘strongly agree’. The total score of this scale varies from 17 to 68, wherein a high score reflects high levels of kinaesthetic phobia.(Aguiar et al., 2017) The TSK has been confirmed to have acceptable reliability (ICC = 0.86) and excellent validity (Cronbach’s α = 0.74).(Wei et al., 2015)

8. The Fear Avoidance Beliefs Questionnaire (FABQ) was used to evaluate fear avoidance belief. The FABQ consists of 16 items, including 2 subscales that are used to evaluate the effects of fear avoidance beliefs on physical activity (items 1–5) and work (items 6–16). Each item is scored from 0 to 6. These scores correspond to strongly disagree, very disagree, disagree, uncertainty, agree, very agree and strongly agree. The total score of this scale ranges from 0 to 96. High scores indicate strong fear avoidance belief.

9. Minimal clinically important difference (MCID) was used to determine whether the treatment produces a significant clinical improvement in pain (NRS) and function (RMDQ). The definition of MCID is ‘the smallest difference or change in a clinical outcome that is perceived as beneficial to patient’s medical management, assuming no excessive side effects and costs’.(Fishbain, Gao, Lewis, & Zhang, 2016) MCID is an evidence-based assessment tool for behavioural interventions across an entire procedure.(Grant, Pedersen, Osilla, Kulesza, & D'Amico, 2016; Lee et al., 2017) A reduction of 2 or more in the NRS indicates positive clinical change.(Ostelo et al., 2008) And several studies have recommended that the MCID for RMDQ-24 is the absolute cut-off of 5 points.(Lee et al., 2017; Ostelo et al., 2008)

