| The Minimal Clinically Important Difference (MCID) |  | ✖ | ✖ | ✖ |
| Global Perceived Effect (GPE) |  | ✖ | ✖ | ✖ |
| Adverse Events |  | ✖ | ✖ | ✖ |
| Recommendation |  | ✖ | ✖ | ✖ |

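### The 5-point RMDQ responder rule is out of reach for anyone entering at RMDQ 0–4, and the unadjusted chi-square ignores the baseline score that decides who can respond

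*Protocol*

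**What the plan says.** Four places in the Protocol bear on this point.

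- **Scale.** Under Primary outcomes, the RMDQ has 24 yes/no items: "The final score varies from 0 to 24", with higher scores worse.
- **Threshold.** Under Secondary outcomes, item 9, the Protocol states that "several studies have recommended that the MCID for RMDQ-24 is the absolute cut-off of 5 points". The Statistical analysis section repeats the RMDQ and NRS thresholds: "values of 5.0 and 2.0 are considered reasonable and commonly used". Neither place gives a percentage alternative, a rule for low baselines or a restricted denominator.
- **Test.** The Statistical analysis section says: "A chi-square test was conducted to compare the proportion of participants in each group who met the MCID for pain and function at postintervention". No covariates are attached to this test. The adjustment factors in that section belong to the repeated measures ANOVA, and baseline RMDQ is not among them.
- **Entry.** The only severity threshold in the inclusion criteria is a worst-pain NRS of at least 3. Neither the inclusion nor the exclusion criteria set a minimum RMDQ.

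Table 3 marks MCID at 3, 6 and 12 months, whereas the test is planned only at the end of the intervention.

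**The concern.** A score bounded at 0 cannot fall by more than its starting value. An absolute fall of 5 points is therefore impossible for some eligible participants, and baseline RMDQ decides who they are. The planned test compares raw proportions and takes no account of that baseline.

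Item 9 uses the MCID to judge whether treatment brings a clinically important improvement in function. Every participant who cannot respond adds to the denominator and never to the numerator, in either arm. The observed risk difference then understates the difference among those who could respond, and the test loses power. A chance imbalance between arms in the share of low entrants also adds noise that an adjusted comparison would remove.

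Separately, the Protocol schedules the MCID at two follow-up visits for which it plans no between-group responder comparison.

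**Working it through.** The Protocol gives no figure for the responder comparison, so there is none to reproduce. The 5-point rule is read as a fall from baseline. Item 9 implies this by defining the MCID as a difference or change, but does not spell it out for the RMDQ.

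**Step 1. Who can respond.** Maximum possible fall = baseline RMDQ.
- Baseline 0–4: the maximum fall is 0–4, below 5, so response is impossible. Going from 4 to 0 is a change of 4 and counts as non-response.
- Baseline 5: response only by falling to 0.

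**Step 2. How many.** No baseline RMDQ distribution is given, so this step rests on assumption. For a normal distribution with continuity correction, the share at 4 or below is Φ((4.5 − mean)/SD).

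| Assumed baseline mean | SD 3 | SD 4 | SD 5 |
| --- | --- | --- | --- |
| 6 | 31% | 35% | 38% |
| 8 | 12% | 19% | 24% |
| 10 | 3% | 8% | 14% |
| 12 | 1% | 3% | 7% |

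Example: mean 8, SD 4 gives Φ(−3.5/4) = Φ(−0.875) = 0.19, or about 9.5 of 50. A beta-binomial on 0–24 gives similar or somewhat higher shares at the low means, up to 47% at mean 6, SD 5.

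**Step 3. Effect on the comparison.** Let q be the share who cannot respond. If the responder rates among the rest are p₁ and p₂, the rates among all randomised are (1 − q)p₁ and (1 − q)p₂. The risk difference is therefore multiplied by (1 − q).

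Power, with p̄ the mean of the two rates, is Φ{[|p₁ − p₂| − 1.96√(2p̄(1 − p̄)/n)] / √[p₁(1 − p₁)/n + p₂(1 − p₂)/n]}.

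Assume 50% and 25% among those able to respond, and take n = 50 per arm from Sample size calculation.
- q = 0: p̄ = 0.375, so (0.25 − 0.190)/0.0935 = 0.64 and power is 0.74.
- q = 0.20: rates 0.40 and 0.20, p̄ = 0.30, so (0.20 − 0.180)/0.0894 = 0.23 and power is 0.59.
- q = 0.35: rates 0.325 and 0.1625, difference 16 points, power 0.47.

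Restricting to those able to respond gives 0.64 at q = 0.20 (40 per arm) and 0.55 at q = 0.35 (32.5 per arm). Restriction recovers only part of the loss. At q = 0.03 and 0.08, power with everyone included is 0.72 and 0.68, a small loss from 0.74.

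**Step 4. Chance imbalance.** At q = 0.20, the between-arm difference in the share of low entrants has SD √(2 × 0.20 × 0.80/50) = 0.08, or 8 percentage points.

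**Step 5. Adjustment.** Simulations under assumed baselines compared the chi-square with a comparison adjusted for baseline RMDQ. Adjustment raised power by about 4 to 12 percentage points, with type I error near 5%. The gain depends on how strongly response follows baseline, so it is an order of magnitude only.

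**The case against.** The strongest reply concerns consequence. The MCID proportion is one of twelve secondary outcomes. The primary outcome is the RMDQ score, analysed by repeated measures ANOVA, where a fall from 4 to 0 counts in full; the global perceived effect scale can also register that participant's improvement. Whether someone can respond depends only on a score taken before treatment, so under randomisation the floor falls on both arms alike in expectation. The chi-square keeps its type I error, and the distortion is toward no difference. All of this stands.

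A reader might infer that the responder conclusion is bound to be wrong. The documents do not support that: the result is dilution and lost power, not a false direction.

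A reader might also take the RMDQ means of 5.37 and 6.11 in Sample size calculation as a sign that entry scores will be low. They are scores at the 3-month follow-up of the cited trial, after treatment, in a trial whose title specifies elderly patients. They say nothing reliable about baseline here.

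A reader might add that the 2-point NRS rule does not name which of the four NRS scores it uses. That detail is commonly left to the statistical analysis plan, which is not at hand, so it is not held against the Protocol.

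Finally, the proportion among all randomised participants is a legitimate quantity, and the Protocol commits to intention-to-treat as well as per-protocol analysis. Making a subset the main analysis would trade that away for a modest gain (0.59 to 0.64 in the example). This also stands and shapes the fix.

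What the reply does not remove is that the Protocol itself fixes the threshold, the test and the time point, and that the test ignores a variable already collected that determines who can respond.

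**Conclusion.** The point holds as a weakness of a secondary analysis. That entrants at RMDQ 0–4 cannot meet the rule follows from the Protocol alone, given that the 5 points are a fall from baseline. The size does not: the share affected runs from about 3% to 35% for assumed baseline means of 12 down to 6 with SD 4. At the low end the loss is negligible. At a 20% share, with assumed rates of 50% and 25%, the risk difference shrinks from 25 to 20 points and power from 0.74 to 0.59. Neither the direction of the comparison nor the primary analysis is affected.

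The time-point mismatch between the Statistical analysis section and Table 3 is plain on the text. It does not leave the long-term goal untested, because the group × time ANOVA covers all visits.

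**What to change.** 1. Keep all randomised participants in the main RMDQ responder analysis. Replace the chi-square with logistic regression on arm and baseline RMDQ, and report a standardised risk difference: average the model's predicted response probabilities over all participants under each arm, then subtract.
2. Add a sensitivity analysis in participants with baseline RMDQ of 5 or more. The subset is defined before randomisation, so the comparison within it remains a randomised one.
3. Report the responder comparison at 3, 6 and 12 months, so that the Statistical analysis section and Table 3 agree.
4. State that the 5 points are a reduction from baseline, and report the share in each arm entering at 0–4 so that readers can judge the dilution.

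The cost is wording and a little programming. RMDQ is already collected at all four visits, and neither sample size nor conduct changes. The sensitivity analysis will include fewer participants and is correspondingly less precise.
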